#### Recruitment

To enhance completion of data collection, research staff will email, text and telephone reminders and, if necessary, will complete questionnaires over the phone with the patient. Screening logs will be kept, with a record of missed patients. We will collect non-identifiable data on children presenting to ED with forearm injuries during the study period, including those not recruited, to establish recruitment rates, determine any systematic bias and support interpretation of the economic evaluation.

#### Randomisation

Randomisation to either POCUS or x-ray as the initial diagnostic modality will be computer-generated via a web-based central randomisation service (Griffith University Clinical Trials Randomisation Service). Randomisation will occur in a 1:1 ratio within blocks of size 6–8 (size randomly selected), stratified by site and age (5–9 years and 10–15 years). Secure, password-protected web-based randomisation will occur once; the participants’ eligibility has been confirmed by the clinician and baseline data collected. Randomisation to intervention will be generated by any credentialed clinician available to perform POCUS.

#### Blinding

This is an open-label trial. However, radiographers performing the x-rays, and radiologists or trainees reporting them, will be masked to the original diagnostic allocation of patients and any POCUS images. The expert panel determining the final diagnosis will be masked to the primary and secondary outcomes.

## Data collection and management

Data will be manually collected at the initial hospital visit, later manually entered into the secure, purpose-built web-based database, REDCap® (Research Electronic Data Capture, Vanderbilt University, Nashville, TN, USA), and then via automated electronic surveys directly linked to the database, emailed to participants after discharge at the designated timepoints, generally a combination of 1, 4 and 8 weeks (Figs. 1 and 2). If the electronic surveys have not been returned, parents will receive a phone call within 48 h to remind them to complete and submit them. A maximum of 5 attempts to contact parents or secondary contacts by either telephone, text message or email will be made by the research team. If there is no response after the 5th attempt, the participant will be considered lost to follow-up for that time point but will still be contacted at subsequent time points, unless the patient withdraws from the trial.

**Fig. 2 Fig2:**
[figure not shown]
Recruitment and data collection flowchart

### Demographics

Patient demographic and clinical characteristics will be recorded, including hand preference, injured arm, mechanism of injury, time of injury, previous forearm issue (injury, surgery, dysfunction) and analgesia provided (home and in ED).

### Functional outcome

The PROMIS is a validated tool that assesses the physical function, including activities of daily living, for patients 5–17 years of age [21–23]. This tool is an 8-item survey, with each item measured on a 5-point scale. It is self-reported from 8 years old and proxy-reported (i.e. parental assistance) below 8 years, reflecting function during the previous 7 days and takes up to 10 min. It should be completed each time in the same setting, ideally in a quiet location in their own home. The duration of immobilisation, including splint or casting, will be compared between the trial arms using data from the Costs & Management Survey and the medical record.

### Health care costs

For the healthcare sector perspective analysis, the sum cost of direct healthcare resources, including implementation, staff labour, equipment and ED length of stay, will be estimated per patient for both study arms. A bottom up a costing methodology will be adopted that specifically measures resource use (i.e. number and type of diagnostics, treatment time and consumables) as well as costs associated with implementation including training. Health resource use during initial procedure will be extracted from individual electronic medical records. Data of resource use for implementation will be collected during the trial by research staff. For the societal perspective analysis, healthcare utilisation beyond the initial procedure, patient and parent time, travel and other indirect health care costs will be collected using the Cost & Management questionnaire adapted for use in this study [24]. Parent time off work and school or childcare absence, due to original injury, will be recorded for use in the societal economic evaluation. Healthcare utilisation will include return visits to the emergency department, outpatients or other practitioners, additional imaging and admission to hospital.

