#### Sample size

Sample size calculations were based on a non-inferiority hypothesis comparing POCUS with x-ray (routine care) for the primary outcome of upper limb function assessed using the PROMIS score at 4 weeks. Previous studies suggest the true between-group difference was assumed to be zero with the non-inferiority margin defined as an absolute difference of 5 points and the standard deviation of PROMIS assumed to be 11.5 points [21–23]. To achieve 90% power with a one-sided α of 0.025, we require primary outcome data for 224 children (112 per arm).

A key secondary endpoint is to assess the non-inferiority of POCUS compared with x-ray as the initial imaging strategy for children who are later confirmed by the expert panel to have buckle fractures. Previous studies suggest that the standard deviation of PROMIS for children with buckle fractures is approximately 7.5 points [21–23]. Assuming the true between-group difference is 0 and defining the non-inferiority margin as 5 points, then with 90% power and one-sided *α* = 0.025, we require primary outcome data on 96 children with buckle fractures (48 per arm). We assume 35–45% of participants will be diagnosed with buckle fractures by the expert panel.

Recruitment will continue until primary outcome data has been collected on both at least 112 children per arm and at least 48 buckle fractures per arm. Allowing for approximately 25% attrition and variation in buckle fracture prevalence, we expect to recruit up to 300 patients to achieve the required sample size.

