### Complications

Complications will be compared across the two trial arms and will include the diagnosis of an alternative fracture pattern to the initial diagnostic imaging, worsening fracture deformity, rates of re-injury, growth disturbance, delayed fracture healing and/or the requirement for surgical intervention. This information will be obtained from the Costs & Management survey and from the electronic medical record.

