### Statistical methods

Summary statistics will be presented as either mean (SD) or median (25th–75th percentile) for continuous data, depending on their distribution, and as frequency (percentage) for categorical data. For the primary outcome, physical function assessed by the PROMIS tool at 4 weeks, we assess non-inferiority of POCUS within a 5-point margin. The between-group difference at 28 days will be assessed using linear regression modelling with treatment group (POCUS/x-ray) included as a main effect. Non-inferiority will be established if the 95% confidence interval for the difference between-groups is completely above the non-inferiority margin. Primary analyses will include all randomised patients. A secondary analysis of the subgroup of patients confirmed to have buckle fractures by the expert panel will be undertaken. Analysis will be on an intention-to-treat basis, with a secondary per-protocol analysis undertaken.

Secondary outcomes such as costs, satisfaction, pain, complications, rates of imaging, length of stay and diagnostic accuracy for the two study groups will be compared. Linear regression models will be used to compare continuous outcomes, logistic regression models will be used to compare dichotomous outcomes, and Poisson regression models will be used to compare count outcomes. Subgroup analyses will be performed for each category of ‘no’ fracture, ‘buckle’ fracture and ‘other’ fracture, and also for age category (5–9 and 10–15 years), given that healing rates may differ in these age groups. Missing data will not be imputed.

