#### Health economic analysis

For the economic evaluation, a cost-utility analysis will be conducted from both the healthcare sector and broader societal perspective. The primary outcome will be the incremental cost per quality adjusted life year gain. From the healthcare sector perspective, only direct health care costs will be included. For the broader societal perspective costs will also include indirect costs associated with work absenteeism and travel. Analyses from both perspectives will use quality-adjusted life years as the primary measure of benefit. Supplementary analyses will also provide the cost per PROMIS unit improvement and cost per x-ray avoided. Primary calculation of quality-adjusted life years will be estimated using an area under the curve approach [28]. Secondary analysis of quality-adjusted life years will estimate change in health-related quality of life over time using multi-level regression modelling with a random intercept, including time as a repeated categorical variable and adjusting for baseline scores [29]. As costs and QALYs are usually non-normally distributed [30], we will use generalised linear regression models (a priori assuming log link and gamma error which will be tested during analysis using the Pregibon link test and modified Park’s test). The 95% confidence interval estimated using the multi-level regression approach for quality adjusted life years will be presented. Uncertainty in the incremental cost per quality-adjusted life year estimate will be assessed using bootstrapping (minimum 1000 iterations) for probabilistic sensitivity analysis with 95% credible interval being reported. The incremental cost per quality-adjusted life year will be compared against a threshold willingness to pay value of $50,000 (a commonly used threshold in Australian cost–utility studies) with the sensitivity to decision making of this threshold value assessed using a cost-effectiveness acceptability analysis [31].

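### Later hospital use is costed from a parent questionnaire alone, although the trial already reads the medical record after discharge; naming the record as a source would be a cheap gain in completeness

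*Protocol article*

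**What the plan says.** The source of cost data changes at ED discharge. For the index visit, the Health care costs section states: "Health resource use during initial procedure will be extracted from individual electronic medical records". For everything later, it states under the societal analysis that "healthcare utilisation beyond the initial procedure, patient and parent time, travel and other indirect health care costs will be collected using the Cost & Management" (a parent-completed form), and then defines the later items: "Healthcare utilisation will include return visits to the emergency department, outpatients or other practitioners, additional imaging and admission to hospital". It names no other source for them.

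Elsewhere the protocol uses the record after discharge. The Complications section, which covers changed fracture diagnosis, worsening deformity and surgery, states: "This information will be obtained from the Costs & Management survey and from the electronic medical record". The Functional outcome section likewise combines the survey with the medical record for duration of immobilisation. The Management section books the 1-week review of children with no fracture or a buckle fracture at the site that first treated them, with x-ray there if clinically indicated. The Rates of imaging section names no source.

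On missing data, the Sample size section plans recruitment with this allowance: "Allowing for approximately 25% attrition and variation in buckle fracture prevalence". The Statistical methods section adds: "Missing data will not be imputed". Neither the costing section nor the Health economic analysis section says how a child with index costs but no questionnaire enters the analysis.

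**The concern.** The arms are designed to differ on either side of the point where the source changes. Any saving from an avoided x-ray or an earlier discharge with POCUS falls in the index visit, which the record captures for nearly every child. Any delayed x-ray, return visit or treatment of a missed fracture falls afterwards, where capture depends on a family returning a form.

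Cost matters in this trial. The Objectives section hypothesises an overall reduction in x-rays and costs. The Discussion says that, if POCUS is non-inferior, the choice of imaging will rest mainly on cost, patient preference and pain. Cost per x-ray avoided is a planned supplementary result. For hospital events, much of the information would already sit in a record that the trial opens for another outcome.

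**Working it through.** **1. The plan's own figures.** Inputs from the Sample size section: margin 5, SD 11.5, true difference 0, one-sided alpha 0.025, power 90%, attrition about 25%.
- Per arm: 2 × (1.960 + 1.282)² × (11.5/5)² = 2 × 10.507 × 5.29 = 111.2, rounded up to 112, as stated; 224 in total.
- Recruitment: 224/(1 − 0.25) = 298.7, rounded up to 299, against up to 300 stated.
- 300 − 224 = 76 children (25.3%) without primary outcome data.

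The 25% is therefore an allowance for the 4-week primary outcome. The protocol gives no non-return rate for the cost questionnaire. Below, f is the share of children without usable later data. It is assumed to be 25%, with a range of 10% to 35%.

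**2. Children affected.** 300 × f = 75 (30 at 10%, 105 at 35%).

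**3. If these children are dropped.** Their index cost goes too. The expected cost difference is unchanged if missingness is unrelated to cost. The standard error grows by 1/√(1 − f):
- f = 10%: 1.05
- f = 25%: 1.15
- f = 35%: 1.24

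If non-responders differ, the result describes responders. For example, assume that they re-attend at twice the responders' rate r. The true rate is 0.75r + 0.25 × 2r = 1.25r, and the reported rate r is 20% too low.

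**4. If a blank adds nothing to the per-child sum.** Let S be the index saving with POCUS, C_P and C_X the mean later costs with POCUS and x-ray, and f_P and f_X the shares missing.
- True net saving = S − (C_P − C_X).
- Counted net saving = S − [(1 − f_P)C_P − (1 − f_X)C_X].
- Error (counted minus true) = f_P·C_P − f_X·C_X.

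No unit costs are given, so S = 100 is an assumption. With equal missingness and L = C_P − C_X, the error is f × L:

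| L | f | True net saving | Counted |
|---|---|---|---|
| 0 | 25% | 100 | 100 |
| 50 | 25% | 50 | 62.5 |
| 100 | 10% | 0 | 10 |
| 100 | 25% | 0 | 25 |
| 100 | 35% | 0 | 35 |
| −50 | 25% | 150 | 137.5 |

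The sign of the net result is wrong only if L lies between S and S/(1 − f), that is, between 100 and 133 at f = 25%. With equal later costs of 100 per child and missingness of 30% with POCUS against 20% with x-ray, the error is 30 − 20 = 10 in favour of POCUS. With the shares reversed, it is 10 against.

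**5. Which results the record can help.** It can supply hospital visits, imaging and admissions, and so hospital cost totals, imaging counts and cost per x-ray avoided. It cannot supply CHU9D utilities, travel, time off, or care outside the hospital record.

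**The case against.** A reader might infer that attrition of 25% strips out later visits and imaging while leaving the index saving intact, so that the plan overstates the saving from POCUS. The documents do not support that reading, for four reasons.
- Nothing says that an unreturned questionnaire counts as zero cost. Filling blanks with zero is a form of imputation, which the Statistical methods section arguably rules out, and a complete-case analysis would drop the index cost as well.
- The direction is not given. Children with no fracture or a buckle fracture have the same 1-week review in both arms. With equal later costs and equal response, even counting blanks as zero gives no error.
- The 25% is a recruitment allowance, worded together with variation in buckle prevalence. The Recruitment section allows completion by phone. The Data collection and management section allows up to five contact attempts and treats non-response as loss for that time point only. A child who misses one survey may return another.
- The primary economic result is cost per QALY, and QALYs need the CHU9D. A family that returns no survey lacks follow-up utilities, however complete the record is.

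It can also be said that a questionnaire reaches other practitioners and other facilities, which a hospital record does not, and that a condensed article need not carry every costing rule.

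The four limits stand, and they keep the point modest. The last two arguments do not remove it. The questionnaire can be kept for what only it can reach. The article does not leave the source open: it names one for later use, and a narrower one than it names for complications.

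**Conclusion.** The point holds as a cheap improvement in data completeness, not as a demonstrated bias. For costs, later hospital use rests on a parent questionnaire alone, while the same protocol already reads the record after discharge for other outcomes. With some non-response and no imputation, later use will be less complete than index use.

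The size depends on an unstated non-return rate and an unstated handling rule. At the assumed 25%, dropping the affected children costs about 15% in interval width and leaves cost results resting on responders. Counting blanks as nothing shifts the net cost difference by a quarter of the later between-arm difference, in whichever direction that difference runs, and more or less if response differs by arm. The monetary figures in the working are illustrations on an assumed index saving of 100. The benefit of a change falls mainly on healthcare cost totals, imaging counts and cost per x-ray avoided, and only partly on cost per QALY. The primary outcome and the sample size are unaffected.

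**What to change.** In the Health care costs section, state that return ED visits, hospital outpatient visits, imaging and admissions up to 8 weeks will be extracted from the electronic medical record for every randomised child, whether or not surveys are returned. Do this in the record review already planned for complications. Keep the questionnaire for non-hospital practitioners, care at other facilities, travel, and time off work or school.

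In the Rates of imaging and Health economic analysis sections, name the record-based imaging count, supplemented by the survey, as the source for imaging rates and cost per x-ray avoided.

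The cost is a change of wording, a few more extraction fields and slightly more extraction time. Care at facilities outside the record would still be known only from the survey, and QALYs would still depend on CHU9D response.

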### Health-related quality of life

Data on health-related QOL will be gathered from the Child Health Utility 9D (CHU9D) tool [25] and scored using the Australian utility algorithm [26]. The CHU9D is a 9-item questionnaire that can be administered in less than 5 min, with self-reported from 7 years old and proxy-reported below 7 years, based on the child ‘today’. CHU9D adolescent weightings will be applied to the analysis, with estimation of quality adjusted life years for both study arms.

### Satisfaction

Patient and parent satisfaction scores based on a 5-point Likert scale (Fig. 3) will be collected. Patients and parents will be independently asked to rate their level of satisfaction.

**Fig. 3 Fig3:**
[figure not shown]
Patient and parent satisfaction rating scales

### Pain

Faces Pain Score Revised (FPSR) is a reliable and validated tool for assessment of pain in children in the age range for this trial, with scores based on the patient’s current level of pain [27].

### Complications

Complications will be compared across the two trial arms and will include the diagnosis of an alternative fracture pattern to the initial diagnostic imaging, worsening fracture deformity, rates of re-injury, growth disturbance, delayed fracture healing and/or the requirement for surgical intervention. This information will be obtained from the Costs & Management survey and from the electronic medical record.

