#### Pocus

Eligible patients randomised to POCUS will have imaging performed by a health practitioner (nurse, doctor or allied health professional) who has undergone training and credentialing. Credentialing consists of a 2-h simulated training package with a phantom arm model [16], followed by proctored scanning, the collection of a logbook of scans demonstrating a total of 20 patients with a mixture of at least 10 buckle or cortical breach fractures, image interpretation from a bank of case examples and a final observed assessment. A modified 6-view forearm POCUS protocol will be conducted, whereby the distal radius and ulna are interrogated on their dorsal, lateral and volar aspects with a high frequency linear probe in a longitudinal axis with the probe marker orientated distally [10]. Secondary signs will also be assessed (Table 2), which includes the pronator quadratus haematoma sign [19]. Patients will be provided with analgesia as required and rest their forearm, ideally on a pillow, during the procedure. Pain will be minimised by use of gel and minimal probe pressure. The final image(s) will be prospectively labelled with the overall forearm diagnosis, being as specific as possible for the cortical breach subtype.

**Table 2 Tab2:** Criteria for consideration of x-ray imaging after POCUS

POCUS Primary sign	
• Identification of a cortical breach fracture (apart from an isolated ulna styloid fracture or non-displaced, non-angulated ulna metaphyseal fracture)	
POCUS Secondary signs:	
• Buckle fracture < 1 cm from physis	
• Pronator quadratus haematoma present (i.e. positive fat pad sign)	
• Angulation greater than ~ 5 degrees (visually angulated)	
• Physis widened or narrowed	
• Periosteal haematoma	
Clinical basis	
• Clinical suspicion, despite normal POCUS findings e.g. ‘pain out of proportion’ as per clinician judgement	

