Patients will receive an overall forearm diagnosis based on the POCUS findings and be classified into 3 fracture categories: ‘no’, ‘buckle’ or ‘other’. A ‘buckle’ fracture is defined as an inward or outward deformation of bone cortex without breach. The ‘other’ fracture group will consist of any fracture with a cortical breach identified using POCUS. A cortical breach is defined as a break, step or gap in the bone cortex. Both the radius and ulna bones will be individually classified, with the overall forearm classification based on the overarching fracture that determined the management of the patient (Table 3). If classified as ‘other’ fracture on POCUS, they will receive an x-ray and be managed on that basis. If either ‘no’ or ‘buckle’ fracture is identified on POCUS, the patient will not receive an x-ray prior to discharge. Ulna styloid, or non-displaced, non-angulated ulna metaphyseal fractures will be considered clinically insignificant and can be managed conservatively in a wrist splint. Both the x-ray and POCUS images will be later reviewed for correct fracture classification and clinical relevance by an expert panel.

**Table 3 Tab3:** Overall fracture diagnosis group classifications

‘No’ fracture	
• No fracture of the radius or ulna	
‘Buckle’ fracture	
• Buckle fracture of the distal third radius, with or without:	
- Ulna styloid fracture	
- Ulna metaphysis non-displaced/non-angulated buckle or cortical breach fracture.	
• Isolated buckle fracture of the distal third ulna	
‘Other’ fracture	
• Cortical breach fracture of the distal third radius (including greenstick, complete or physeal), with or without any ulna fracture type	
• Any isolated displaced/angulated cortical breach fracture of the ulna metaphysis	
• Fractures at other locations, e.g. proximal radius, scaphoid	
• Bowing fractures of the radius and/or ulna with or without any other fracture type	

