#### Criteria for discontinuing or modifying allocated interventions

X-ray will be performed as per usual practice, with views limited by patient tolerability. Inadequate views may require repeating, as per clinician judgement. Although it is unusual to be unable to obtain x-rays, if this occurs, reasons will be documented. POCUS will be discontinued if the patient experiences undue distress or excessive pain whilst POCUS is performed, or if adequate images are unable to be obtained, and will receive x-rays instead. If classified as ‘other’ fracture on POCUS, such as identification of a cortical breach, they will receive an x-ray and be managed accordingly. Patients may also receive x-rays based on secondary signs of a cortical breach fracture detected on POCUS or ‘pain out of proportion’ as per treating clinician judgement. Full criteria for x-ray imaging consideration after POCUS are listed in Table 2. Patients who subsequently receive x-rays will receive routine cares based on its findings.

Once the initial diagnostic test (POCUS or x-ray) has been conducted, the intervention will be considered complete. Patients will receive analgesia as required, which will be documented for comparison between diagnostic arms and subgroups. The trial has been designed to safeguard against any clinically significant fractures being missed in either study arm. The extended POCUS protocol is designed to utilise secondary signs, such as the pronator quadratus haematoma sign, which shows promise as an additional measure to avoid missing any cortical breach fractures [19]. Furthermore, the follow-up review, if required, is an appropriate timeframe to intervene for any missed fractures. All patients with a displaced or angulated fracture of significance will receive orthopaedic specialist care, including during and after the trial. Any deviation from the protocol will be noted, specifically if this changed fracture management.

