### Outcomes

#### Trial endpoints

The primary outcome is upper limb physical function at 4 weeks (28 days ±3 days) as measured by the validated Pediatric Upper Extremity Short Patient-Reported Outcomes Measurement Information System (PROMIS) tool. This timeframe was chosen, as patients with buckle fractures and soft tissue injuries should have regained normal physical function by this time, compared with cortical breach fractures. Provided there are no re-injuries, 8 weeks is an accepted time frame for fracture healing in children, with recovery of function within 3–4 weeks for children with distal forearm buckle fractures [20]. The earlier follow-up period as the primary outcome is designed to detect any difference of arm function between diagnostic groups, with complications being a secondary outcome.

Health economic analysis will be conducted to determine the cost-effectiveness of POCUS compared to x-ray with the main outcome being the incremental cost per quality adjusted life year from both a health care sector perspective and broader societal perspective. Refer to Table 4 for complete primary and secondary outcomes. Data will be collected at designated time points across an 8-week period (Fig. 1, SPIRIT participant timeline).

**Table 4 Tab4:** Outcome measures for POCUS and x-ray trial arms

Primary outcome measure:	
• Physical function of injured upper limb at 4 weeks (28 ± 3 days), as determined by the PROMIS tool.	
Secondary outcome measures:	
• Direct and indirect health care costs (healthcare provider visits, days off work/school)	
• Health related quality of life (QOL), as determined by the CHU9D	
• Satisfaction score (patient and parent)	
• Patient pain score measured using the FPSR	
• Rates of complications (alternate fracture diagnosed, poor fracture healing)	
• Rates of x-ray and other imaging (particularly the ‘no’ and ‘buckle’ fracture groups)	
• ED length of stay (triage to ED discharge)	
• Treatment time (clinician review to ED discharge)	
• Diagnostic accuracy of POCUS, including secondary signs, and x-ray	

Key: *PROMIS* Pediatric Upper Extremity Short Patient-Reported Outcomes Measurement Information System, *CHU9D* Child Health Utility 9D, *FPSR* Faces Pain Score Revised

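### The complication item is measured against the first imaging test with no time limit, so a pattern change found by the POCUS arm's planned same-visit x-ray can be counted as a complication

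*Protocol article*

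**What the plan says.** **The outcome.** The Complications section states that "Complications will be compared across the two trial arms" and that these "will include the diagnosis of an alternative fracture pattern to the initial diagnostic imaging, worsening fracture deformity", followed by re-injury, growth disturbance, delayed healing and surgery. On sources it says: "This information will be obtained from the Costs & Management survey and from the electronic medical record". Table 4 (Trial endpoints) lists the secondary outcome as "Rates of complications (alternate fracture diagnosed, poor fracture healing". Neither place gives a start time or sets aside imaging done during the index visit.

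**The POCUS pathway.** The Interventions section allocates each child to one initial modality. The section on discontinuing or modifying interventions treats the intervention as complete once that first test is done. The Pocus section then says: "If classified as ‘other’ fracture on POCUS, they will receive an x-ray and be managed on that basis". The discontinuation section repeats that children with an 'other' result, "such as identification of a cortical breach, they will receive an x-ray and be managed accordingly", and adds: "Patients may also receive x-rays based on secondary signs of a cortical breach fracture detected on POCUS". Clinical suspicion or inadequate images can also lead to an x-ray. Scan labels are to be specific, "being as specific as possible for the cortical breach subtype".

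**The x-ray pathway.** The X-ray section plans films only, read by the treating clinician and reported by radiology. It plans no second modality.

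**The concern.** The reference point for an alternative fracture pattern is the first test. In the POCUS arm a second, more detailed test follows by design for a defined group of children, in the same visit and before management is settled. If the film shows a different category from the scan, the screen-then-confirm pathway has worked as intended, yet the wording allows a complication to be recorded.

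The x-ray arm has no planned step that could produce this event. The item is therefore ascertained differently in the two arms for a reason unrelated to harm. A scan corrected before the child leaves would count the same as a fracture first recognised after discharge. That weakens the outcome that bears most directly on the hypothesis, under Objectives, that no clinically significant fracture is missed.

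**Working it through.** **1. The plan's own figures.** The article states no complication rate and no power for complications, so there is nothing to reproduce on this outcome. The group sizes used below do reproduce. For non-inferiority with margin 5, one-sided alpha 0.025 and 90% power, n per arm = 2 × [SD × (1.960 + 1.282) / 5]²:

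- SD 11.5: 111.2, rounded up to 112 (stated: 112).
- SD 7.5: 47.3, rounded up to 48 (stated: 48).
- Attrition: 224 / 0.75 = 298.7, so 299 (stated: up to 300, or 150 per arm).

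**2. The two pathways side by side.**

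| Step | POCUS arm | X-ray arm |
|---|---|---|
| First test (reference for the item) | Scan | X-ray |
| Planned second modality at index visit | X-ray for every 'other'; permitted under Table 2 | None |
| Other index-visit routes to a different pattern | Radiology report of that x-ray | Radiology report, repeat views |
| After discharge ('no' and 'buckle') | Tentative review at about 1 week, x-ray on clinical suspicion | Same |

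The rows differ in the planned second modality. The medical record is a named data source and covers the index visit, so nothing in the stated sources keeps these events out.

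**3. Illustrative size.** Excess in the POCUS arm = P(scan 'other') × P(x-ray pattern differs, given 'other'). Neither input is in the article. Assume 15–35% for the first and 5–30% for the second.

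- Low: 0.15 × 0.05 = 0.75 percentage points; × 112 = 0.8 children (× 150 = 1.1).
- Middle: 0.25 × 0.20 = 5.0 points; × 112 = 5.6 (× 150 = 7.5).
- High: 0.35 × 0.30 = 10.5 points; × 112 = 11.8 (× 150 = 15.8).

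The x-ray arm gains 0 by this route. X-rays under Table 2 in children not labelled 'other' are left out of the product.

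**4. What that could do to the comparison.** Assume also a true rate of 3% in both arms and 112 per arm. The chance of a two-sided p < 0.05 against POCUS from the artefact alone is Φ[(d − 1.96 × se0) / se1], where d is the excess, se0 the pooled and se1 the unpooled standard error. Middle case: d = 0.05, rates 0.08 and 0.03, pooled 0.055.

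- se0 = √(0.055 × 0.945 × 2/112) = 0.0305
- se1 = √[(0.08 × 0.92 + 0.03 × 0.97)/112] = 0.0303
- Φ[(0.05 − 0.0597)/0.0303] = Φ(−0.32) = 37%

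The low case gives about 5% and the high case about 82%. This is a normal approximation, and events are few.

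**The case against.** The strongest reply is that the item should be read in context. Its neighbours in the list are follow-up events. One of its two sources is a survey that the Health care costs section uses for care beyond the initial procedure. The safeguards described in the discontinuation section include a follow-up review for missed fractures. On that reading the item means a fracture recognised later, and event windows are often left to a fuller document. This shows that the intended meaning may be sound. It does not remove the problem, because the article does fix a reference point, and that reference point is the allocated test. With the medical record as a source, a data collector following the text could count the planned x-ray.

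Several stronger readings are tempting, and the article does not support them:

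- **That only the POCUS arm can have this event.** In the x-ray arm a differing radiology report, repeat views or the 1-week review can also yield an alternative pattern. The asymmetry is confined to the planned second modality.
- **That every discordant x-ray counts.** The article does not define whether 'other' changing to 'no', or a change of subtype within 'other', is an alternative fracture pattern. Its formal classification has three categories.
- **That label changes are pooled with harms in one score, or plainly counted twice.** Pooling is not stated, and Diagnostic accuracy measures each test against the expert panel, not against later imaging.
- **That errors leaving the ED go undetected in one arm.** The follow-up rule for 'no' and 'buckle' children is the same in both.
- **That the artefact would decide the comparison.** That is likely only at the upper end of assumed inputs.

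It also stands that this is one secondary outcome with no stated power, and that the bias runs against POCUS, so it cannot create a false claim of non-inferiority on the primary outcome.

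**Conclusion.** The concern holds as a defect of definition in a secondary safety outcome. As written, a category change found by the POCUS arm's planned same-visit x-ray can be recorded as a complication, and the x-ray arm has no planned counterpart. The comparison is open to ascertainment bias against POCUS.

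Its size cannot be known from the article. Under the assumed ranges it is 0.75 to 10.5 percentage points, about 1 to about 12 children per 112, and the low end is negligible. The result rests on two assumed proportions, on a literal reading of the reference point, and on counting every differing x-ray after an 'other' scan as an event. The 3% true rate matters only for the 5% to 82% chance of a nominally significant difference. The PROMIS analysis and the sample size are unaffected.

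**What to change.** In the Complications section and Table 4, define the item identically for both arms: a fracture category (no, buckle or other) diagnosed after index ED discharge that differs from the diagnosis at ED discharge, after all index-visit imaging. Using the three existing categories also settles the status of subtype changes.

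Report same-visit changes from scan to x-ray with Diagnostic accuracy. Report the reclassification item separately from clinical harms such as worsening deformity or surgical intervention.

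The cost is mainly wording. Slightly fewer events will count as complications. The article specifies a reading at discharge only for the x-ray arm, so the POCUS-arm discharge diagnosis must be taken from the medical record where the case report form does not already hold it. No change to the care pathway or the sample size is needed.
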